**2) Trial Hypothesis and Purpose**

(1) Schema

[figure not shown]

(2) Primary Objective

The purpose of this trial is to verify the hypothesis: ‘In comparison to sutures without barbs, using SS-PDS for abdominal fascia closure on female patients who undergo incisional hernia in midline laparotomy due to gynecological diseases will reduce the cumulative incidence of incisional hernia for 1 year after surgery.’

(3) Secondary Objective

A. Compare the incidence curves of incisional hernia over time between A+B arms and C+D arms (depending on whether SS-PDS is used or not).

B. Compare cumulative incidence and types of surgical site infections up to 4 weeks after surgery between A+B arms and C+D arms (depending on whether SS-PDS is used or not).

C. Compare incidence and cumulative incidence of wound dehiscence at Week 4 after surgery between A+B arms and C+D arms.

D. Compare BPI-K scores that are obtained on Day 2 after surgery between A+B arms and C+D arms (depending on whether SS-PDS is used or not)

E. Compare BPI-K scores that are obtained on Day 4 after surgery between A+B arms and C+D arms (depending on whether SS-PDS is used or not)

F. Compare NRS scores that are collected until Day 4 after surgery between A+B arms and C+D arms (depending on whether SS-PDS is used or not)

G. Compare cumulative incidence of surgical site infections and their types until Week 4 after surgery between A+C arms and B+D arms (depending on whether subcutaneous drain was used or not)

H. Compare incidence and cumulative incidence of wound dehiscence between A+C arms and B+D arms at Week 4 after surgery (depending on whether subcutaneous drain was used or not).

I. Compare incidence of adverse events, their type and relevance excluding incisional hernia, pains, surgical site infections, and wound dehiscence between A+B arms and C+D arms.

J. Create a surgical video of abdominal fascia closure using SS-PDS.

1. **Code Names (or Generic Names of Principal Components) of Investigational Product and Medical Device, Raw Material Quantities, Formulation and etc. (including** **comparator)**

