2. Subcutaneous tissue closure is not necessary, but can be performed based on the investigator’s judgment.

3. Skin closure can be performed using stapler or non-absorbent sutures whichever is a general method of each institution.

B. Reasons for the choice

The reasons are stated under the section ‘Background.’

1. **Observation Items, Clinical Test Items, Observation and Test Methods**

| Observation Items | Observation and Test Methods |
| --- | --- |
| 1-year cumulative incidence of incisional hernia after surgery | Subjects are advised to make outpatient visits for Year 1 after surgery. Visits made between 9 and 15 months after surgery can be counted as Year 1 visit. Investigators will conduct a physical checkup to diagnose incisional hernia. Investigators can refer to post-surgery image test result. If investigators are not sure of incisional hernia, a diagnostic test can be carried out. Subjects will be censored if they underwent midline laparotomy once again after receiving the surgery from this study, are dead or lost to follow-up at the time of event. Investigators will not be reminded of group allocation and will be blinded until Year 1 visit is completed. |
| 4-week cumulative incidence and types of surgical site infection after surgery | Subjects are advised to make outpatient visits for Week 4 after surgery. Visits made between 3 to 5 weeks after surgery can be counted as Week 4 visit. Investigators will conduct a physical checkup to diagnose surgical site infection. If subjects make outpatient visits before Week 4 after surgery, investigators should check for surgical site infections and their types. All information obtained from visits made immediately after surgery up to Week 4 will be used to diagnose all surgical site infections. CDC standards will be used to determine surgical site infections and their types. (https://www.cdc.gov/nhsn/PDFs/pscManual/17pscNosInfDef_current.pdf). If any surgical site infection is observed according to CDC standards, the patient will be judged to have a surgical site infection. Investigators will not be reminded of group allocation. |

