| Demographics of subjects, surgical information | Date of birth, height, weight, current smoker, medical history, pre- and postoperative chemotherapy, corticosteroids, previous abdominal surgery, ASA classification, type of surgery, suture length, wound length, operation time, antibiotic prophylaxis, intra-abdominal drain, subcutaneous drain, DVT prophylaxis, Patient controlled analgesia (Y/N, type IV or epidural), wound anesthetics infiltration system, perioperative complications, transfusion, postoperative radiation, ICU care |
| Incidence, types, grades and relevance of adverse events excluding incisional hernia, pains, surgical site infections, and wound dehiscence | Adverse events are collected by listening to the subject’s medical history and conducting a physical checkup during hospitalization for surgery, Week 4 and Year 1 visits after surgery. All visits and medical records until Year 1 after surgery will be used. CTCAE ver 4.0 will be used to grade each adverse event. |

1. **Efficacy Evaluation Standards, Evaluation Methods**

| Purpose | Analysis and Evaluation Methods | Cohorts for analysis |
| --- | --- | --- |
| Compare cumulative incisional hernia incidence until Year 1 after surgery between A+B arm and C+D arm. | Cumulative incidence of incisional hernia of A+B arm will be compared with that of C+D arm using chi-square or Fisher's exact test. P value 0.05 will be used to determine significance. | All patients who undergo surgery. Patients who do not have incisional hernia will be censored at last visit. Incidence will be estimated from time-occurrence curve. |
| Compare incisional hernia incidence curve by time between A+B arm and C+D arm. | Time-occurrence curve of incisional hernia will be depicted using Kaplan-Meier method and be compared between A+B vs C+D arm using log-rank test. P value 0.05 will be used to determine significance. | All patients who undergo surgery |
| Compare cumulative incidence of surgical site infections and their types until Week 4 after surgery between A+B arm and C+D arm. | Cumulative incidence of SSI of A+B arm will be compared with that of C+D arm using chi-square or Fisher's exact test. P value 0.05 will be used to determine significance. Type of SSI will be summarized. | Patients who undergo surgery |

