| Compare cumulative wound dehiscence incidence at Week 4 after surgery between A+B arm and C+D arm. | Cumulative incidence of wound dehiscence of A+B arm will be compared with that of C+D arm using chi-square or Fisher's exact test. P value 0.05 will be used to determine significance. | Patients who undergo surgery and complete week 4 visit |
| Compare wound dehiscence incidence at Week 4 after surgery between A+B arm and C+D arm. | Incidence of wound dehiscence of A+B arm will be compared with that of C+D arm using chi-square or Fisher's exact test. P value 0.05 will be used to determine significance. | Patients who undergo surgery and complete week 4 visit |
| Compare BPI-K scores that are obtained at baseline, Day 2 and Day 4 after surgery between A+B arm and C+D arm. | BPI score (total and each question) obtained at baseline will be compared between A+B vs C+D arm. BPI score (total and each question) obtained at postoperative day 2 will be compared between A+B vs C+D arm. BPI score (total and each question) obtained at postoperative day 4 will be compared between A+B vs C+D arm. Student t-test will be used. P value 0.05 will be used to determine significance. If BPI score at baseline is imbalanced between arms, change of BPI score (from baseline to postoperative day 2, 4) will be compared. | Patient who undergo surgery and complete BPI |
| Compare NRS pain scores collected until Day 4 after surgery between A+B arm and C+D arm. | NRS collected for postoperative 4 days will be compared between A+B vs C+D arm using linear mixed model. P value 0.05 will be used to determine significance. | Patients who undergo surgery and NRS are measured |
| Compare cumulative incidence and types of surgical site infections until Day 4 after surgery between A+C arm and B+D arm (depending on whether subcutaneous drain is inserted or not) | Cumulative incidence of SSI of A+C arm will be compared with that of B+D arm using chi-square or Fisher's exact test. P value 0.05 will be used to determine significance. Type of SSI will be summarized. | Patients who undergo surgery |
| Compare cumulative wound dehiscence incidence at Week 4 after surgery between A+C arm and B+D arm (depending on whether subcutaneous drain is inserted or not) | Cumulative incidence of wound dehiscence of A+C arm will be compared with that of B+D arm using chi-square or Fisher's exact test. P value 0.05 will be used to determine significance. | Patients who undergo surgery and complete week 4 visit |

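### The analysis-table row for the drain comparison of surgical site infection stops at Day 4, whereas the objective, the endpoint definition and the parallel suture row all use Week 4

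*Protocol*

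**What the plan says.** The Protocol states the window for SSI in several places.

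- **Objective.** Under Trial Hypothesis and Purpose, Secondary Objective G reads "Compare cumulative incidence of surgical site infections and their types until Week 4 after surgery between A+C arms and B+D arms".
- **Endpoint definition.** The table under Observation Items, Clinical Test Items, Observation and Test Methods has one SSI item, "4-week cumulative incidence and types of surgical site infection after surgery". It adds that "All information obtained from visits made immediately after surgery up to Week 4 will be used to diagnose all surgical site infections". The visit itself has a tolerance: "Visits made between 3 to 5 weeks after surgery can be counted as Week 4 visit".
- **Analysis table, suture comparison.** Under Efficacy Evaluation Standards, Evaluation Methods, the row reads "Compare cumulative incidence of surgical site infections and their types until Week 4 after surgery between A+B arm and C+D arm".
- **Analysis table, drain comparison.** In the same table the row reads "Compare cumulative incidence and types of surgical site infections until Day 4 after surgery between A+C arm and B+D arm". Its method cell gives no window: "Cumulative incidence of SSI of A+C arm will be compared with that of B+D arm using chi-square or Fisher's exact test". The threshold is a p value of 0.05.

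The row directly above the drain SSI row concerns pain, where Day 4 is the planned limit: "Compare NRS pain scores collected until Day 4 after surgery between A+B arm and C+D arm".

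Item (1) of Data Analysis and Statistical Analysis Methods refers the reader to the efficacy table for the between-group comparisons, so that table is where the analysis is laid down.

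**The concern.** One comparison, drain against no drain on SSI, has two windows. The objective and the endpoint definition say Week 4. The table that sets out the analysis says Day 4. An analyst who follows the table literally would count only infections in the first four days after surgery, and one who follows the objective would count those over four weeks. Each could claim to have kept to the Protocol.

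Drain allocation is also openly disclosed under Control Group Setting and Randomization, item (6). That is a further reason to settle the window before results by drain group are looked at.

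**Working it through.** The Protocol gives no figure to reproduce here. The check is a comparison of texts, followed by simple window arithmetic.

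**Step 1: the statements side by side**

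| Place in the Protocol | Comparison | SSI window |
|---|---|---|
| Secondary Objective G | A+C vs B+D (drain) | Week 4 |
| Observation Items table, SSI item | all subjects | 4 weeks |
| Efficacy table, suture SSI row | A+B vs C+D (suture) | Week 4 |
| Efficacy table, drain SSI row | A+C vs B+D (drain) | **Day 4** |

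The Overview's visit schedule also places the SSI assessment at 4 weeks. No Day 4 SSI endpoint is defined anywhere. In the objectives, measurements and analyses, Day 4 otherwise belongs only to the pain scores (BPI-K and NRS). The analysis population does not mark the drain row as a deliberately different endpoint either, since both SSI rows use patients who undergo surgery.

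**Step 2: how much of the window the literal reading keeps**

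Share kept = 4 days / length of the Week 4 window.

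- Nominal window, 4 × 7 = 28 days: 4/28 = 14.3% kept, and 24/28 = 85.7% dropped.
- Visit at 3 weeks, 21 days: 4/21 = 19.0% kept.
- Visit at 5 weeks, 35 days: 4/35 = 11.4% kept.

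**Step 3: what this says about infections (illustration only)**

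The Protocol states neither an SSI risk nor the timing of onset, so the share of infections caught by Day 4 needs assumptions.

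- *Even onset over 28 days:* 4/28 = 14.3%.
- *Constant hazard with 4-week risk p:* λ = −ln(1 − p)/28, and share = (1 − e^(−4λ))/p. This gives 14.6% for p = 5%, 14.9% for p = 10% and 15.7% for p = 20%.
- *Half of all infections in the first week, evenly spread over it:* 0.5 × 4/7 = 28.6%.

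These results follow from the assumed onset patterns. A pattern with more early onset would give a higher share, and the Protocol offers nothing with which to choose between them.

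**The case against.** The strongest reply is that this is a plain slip that no careful analyst would follow. The wrong words stand only in the column that restates the purpose. The method cell of the same row speaks of cumulative incidence of SSI without a window, and the Protocol defines that quantity over 4 weeks. The pain row directly above ends at Day 4, which suggests a carry-over. No data would be lost, because SSI is recorded to Week 4 in every arm. Only one of ten secondary objectives is touched. The primary hernia comparison, the sample size and the drain stopping rule, which uses wound dehiscence, are not.

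Most of this stands. It shows that the error is probably clerical and cheap to repair, and that its weight is limited. It does not make the row correct: the table is where the Protocol places its comparative analyses, and this row contradicts the objective that it is meant to serve.

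A reader might infer three stronger things, none of which the Protocol supports:

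- **That most infections would be left out.** Most of the *window* is cut. The share of infections depends on onset times that are not given.
- **That the comparison would probably show no difference for lack of events.** No SSI rate and no power for the drain comparison are stated for either window.
- **That Day 4 ends before many drains are out.** The Protocol allows removal from 3 to 14 days, and later in some cases. Some drains could therefore be out by Day 4 and others not, but no distribution of removal times is given.

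**Conclusion.** The point holds as an internal contradiction in the endpoint window of one secondary comparison. The drain SSI row says Day 4 where the objective, the endpoint definition and the parallel suture row say Week 4.

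Its size is 4 of 28 days on a literal reading, or 14% of the nominal window, with a range of 11% to 19% over the permitted visit times. This rests only on the stated windows. The effect on the number of infections counted, or on the result of the test, cannot be determined from the Protocol. The mismatch itself is certain. That it is a slip and not a choice is very likely but is an inference.

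**What to change.** In the drain SSI row of the table under Efficacy Evaluation Standards, Evaluation Methods, replace Day 4 with Week 4, so that the row agrees with Secondary Objective G, the SSI item in the Observation Items table and the suture SSI row. Make the change before SSI results by drain group are examined.

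The cost is a one-word correction. SSI information is already collected to Week 4, so no visit, data item, test or sample size needs to change, and the primary endpoint is unaffected.

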**(1) Discontinuation**

A. The principal investigator can stop the study if it is judged that SS-PDS’s safety is low. Discontinuation of the trial can be considered when serious adverse events occurred from the interim analysis results.

B. The principal investigator can stop the trial if recommended by IRB.

C. The principal investigator can stop the trial if it is impossible to carry out the trial properly.

**(2) Removal of subjects from study**

A. Subjects can remove from study unconditionally while they are participating in the study.

B. Subjects are removed if they do not undergo midline laparotomy. No follow-up will be performed afterwards.

C. If incisional hernia is diagnosed in 4 weeks after surgery, no follow-up will be performed afterwards. In this case, subjects are considered to have completed the trial participation. If incisional hernia is diagnosed when 4 weeks have not elapsed after surgery, follow-up observations will be made until Week 4 after surgery.

D. If subjects undergo another abdominal midline laparotomy after surgery, the subject will be withdrawn from the trial. No follow-up will be performed afterwards.

E. If it is judged that a subject is no longer able to participate in the trial due to the subject’s noncooperation, the principal can decide to discontinue the subject’s participation.

F. If a subject is withdrawn from the trial, data collected until the time of withdrawal are used for the trial.

1. **Evaluation Standards, Methods and Reporting of Safety Including Side Effects**

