| Major Exclusion Criteria | 1. Patients with previous or present abdominal incisional hernia.  2. Pregnant patients.  3. Patients receiving external radiation treatment to the pelvis or abdomen.  4. Patients allergic to PDS components.  5. Patient with diseases that affect wound healing including uncontrolled diabetes, autoimmune vasculitis, and hepatocirrhosis.  6. BMI>35  7. Patients are excluded if they have used or are expected to use drugs that may affect wound healing such as bevacizumab. In case where bevacizumab is used, participation is possible if they have a four-week washout period before and after surgery, respectively.  8. Patients who have had an abdominal midline laparotomy for the last 6 months.  9. If patients had surgery for suspected infection. |
| Efficacy Assessment | The efficacy of SS-PDS will be confirmed if 1-year cumulative incidence of incisional hernia in the experimental group is lower than that of the SS-PDS control group (p value 0.05) |
| Safety Assessment | Comparison of prevalence and grade of adverse events between SS-PDS experimental group and control group. |
| Schedule of Visit/Inspection | Baseline: eligibility check  Surgery: fascia closure with SS-PDS or conventional suture, subcutaneous drain insertion, collecting surgery-relevant parameters, pain level survey after surgery  4 weeks after surgery: surgical site infections and wound dehiscence are studied.  1 year after surgery: incisional hernia is judged. |
| Statistical Methods | Comparison of incidence of incisional hernia between SS-PDS experimental group and control group using Chi-square or Fisher’s exact test. |
| Expected Effects and Results | It is expected that the standard surgical method will be changed to fascia closure using barbed suture.  Incidence of incisional hernia is reduced to improve patients’ quality of life and reduce medical costs. |

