**3) Subcutaneous Drainage Experimental Group**

Jackson-Pratt drain, 7 Fr (Manufacturer to be determined)

**4) Subcutaneous Drainage Control Group :** N/A

1. **Subject Eligibility and Exclusion Criteria, Target Sample Size and Calculation Rationale**
2. **Inclusion Criteria**

(1) Female patients planning to undergo elective midline laparotomy for gynecological diseases.

(2) Over 18 years old.

(3) ECOG performance status 0 - 2

1. **Exclusion Criteria**

(1) Patients with previous or present abdominal incisional hernia.

(2) Pregnant patients.

(3) Patients receiving external radiation treatment to the pelvis or abdomen.

(4) Patients allergic to PDS components.

(5) Patient with diseases that affect wound healing including uncontrolled diabetes, autoimmune vasculitis, and hepatocirrhosis.

(6) BMI>35

(7) Patients are excluded if they have used or are expected to use drugs that may affect wound healing such as bevacizumab. In case where bevacizumab is used, participation is possible if they have a four-week washout period before and after surgery, respectively.

(8) Patients who have had an abdominal midline laparotomy for the last 6 months.

(9) If patients had surgery for suspected infection.

1. **Target Sample Size and Calculation Rationale**

(1) Previous study results were referenced to assume 1-year cumulative incidence of incisional hernia as 0.13 in SS-PDS control group (C+D arm) [PMID: 26188742].

(2) No previous studies have investigated the incidence of incisional hernia after using barbed suture for abdominal fascia closure. Given that there are cases of very low incisional hernia incidence such as 1-2% in previous studies using conventional closure methods, 1-year cumulative incidence of incisional hernia in SS-PDS experimental group (A+B arm) is estimated to be 0.03.

(3) Alpha 0.05 (one-sided), power 0.8, drop-out rate 0.06, each arm (A+B vs C+D): 87 patients

(4) Therefore, the target sample size is 174.

1. **Recruitment Plan**

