**(2) Evaluation Methods**

A. Compare the entire incidence of adverse events that have causal relationship with the SS-PDS use (including control group’s suture) between A+C arm and B+D arm. (significance is judged by p-value 0.05).

B. Compare the incidence of adverse events by type that have causal relationship with the SS-PDS use (including control group’s suture) between A+C arm and B+D arm (significance is judged by p-value 0.05).

C. Compare the entire incidence of grade 3 or above adverse events that have causal relationship with the SS-PDS use (including control group’s suture) between A+C arm and B+D arm (significance is judged by p-value 0.05).

D. Compare the incidence grade 3 or above adverse events by type that have causal relationship with the SS-PDS use (including control group’s suture) between A+C arm and B+D arm (significance is judged by p-value 0.05)

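### The rule that ends follow-up at hernia diagnosis contradicts adverse-event collection to Year 1, so safety observation can be cut short by the primary outcome

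*Protocol*

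**What the plan says.** Under Removal of subjects from study, item C, the protocol states: "If incisional hernia is diagnosed in 4 weeks after surgery, no follow-up will be performed afterwards". It continues: "In this case, subjects are considered to have completed the trial participation". A further sentence covers early diagnoses: "If incisional hernia is diagnosed when 4 weeks have not elapsed after surgery, follow-up observations will be made until Week 4 after surgery". The phrase about 4 weeks in the first sentence is ambiguous in translation. Since the last sentence deals separately with diagnoses before Week 4, the first is best read as covering diagnoses after Week 4.

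The adverse-event row of Observation Items, Clinical Test Items, Observation and Test Methods provides for collection during the surgical admission, at Week 4 and at Year 1. It adds: "All visits and medical records until Year 1 after surgery will be used".

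The suture groups are to be compared on these events. The Overview, under Safety Assessment, plans a "Comparison of prevalence and grade of adverse events between SS-PDS experimental group and control group", and secondary objective I sets A+B against C+D for events other than hernia, pain, surgical site infection and wound dehiscence. The matching row of Efficacy Evaluation Standards, Evaluation Methods takes all operated patients as the cohort and leaves the metric and the test open.

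**The concern.** A patient with a hernia found at month 5 is, under item C, finished with the trial at month 5. Under the observation table she still has a Year 1 adverse-event assessment and a record review to come. Sites cannot follow both instructions, and different sites may choose differently.

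If item C is followed, adverse-event observation stops because the primary outcome has occurred. The trial is built on the expectation that this outcome is more frequent in the control group. Control patients would then be observed for less time on average, their later events would be under-counted, and a suture that prevents hernias would look relatively less safe. The closed period is also the one in which adverse events following the hernia or its repair would arise, and these bear on the protocol's benefit-risk statement. A statistical analysis plan cannot repair this, because the data would not have been collected.

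**Working it through.** **The plan's own figure.** Target Sample Size and Calculation Rationale gives 0.13 (control), 0.03 (SS-PDS), one-sided alpha 0.05, power 0.80, dropout 0.06 and 87 per group. The arcsine formula reproduces it:

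- h = 2·asin(√0.13) − 2·asin(√0.03) ≈ 0.39
- n = 2·((1.645 + 0.842)/h)² ≈ 81.5
- 81.5/0.94 = 86.7, hence 87

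So 87 per group is the right denominator for the planning rates.

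**Patients who could be affected.**

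- Control: 87 × 0.13 = 11.3
- SS-PDS: 87 × 0.03 = 2.6
- Difference: 8.7, so up to about 9 more control patients
- Total: 13.9, so about 14 patients

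These are upper limits, because a hernia cuts observation short only if it is diagnosed before the Year 1 visit. That visit (months 9 to 15 accepted) is the only scheduled hernia assessment after Week 4. Earlier diagnosis is nevertheless foreseen: investigators may use postoperative imaging, and a Kaplan-Meier comparison over time is planned.

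**Size of the distortion.** The documents give neither an adverse-event rate nor the timing of hernia diagnosis, so both are assumptions here. Let p be the true 1-year adverse-event risk, equal in both groups and unrelated to hernia. Assume a constant hazard λ = −ln(1 − p), capture that stops at diagnosis, and a comparison of crude proportions. Then:

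spurious excess in SS-PDS = (0.13 − 0.03) × (p − risk captured in hernia patients)

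Example with p = 0.40 and diagnoses spread evenly from Week 4 to Week 52 (w = 4/52 = 0.077):

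- λ = 0.511
- mean event-free probability at diagnosis = (e^(−λw) − e^(−λ)) / (λ(1 − w)) = (0.961 − 0.600)/0.472 = 0.767
- captured risk = 1 − 0.767 = 0.233
- excess = 0.10 × (0.400 − 0.233) = 0.0167, or 1.7 points

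The same calculation over the assumed range, in percentage points:

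| Hernias diagnosed | p = 20% | p = 40% | p = 60% |
|---|---|---|---|
| all at month 12 | 0 | 0 | 0 |
| all at month 9 | 0.5 | 0.8 | 1.0 |
| evenly, Week 4 to Week 52 | 0.9 | 1.7 | 2.3 |
| all at Week 4 (extreme) | 1.8 | 3.6 | 5.3 |

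With even spread, captured person-time is 1 − 0.13 × 0.4615 = 94.0% in control and 1 − 0.03 × 0.4615 = 98.6% in SS-PDS. The chance of a falsely significant SS-PDS excess rises from a nominal 2.5% to about 3.5% to 5%.

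If hernia rates are equal, the first factor is zero and so is the excess. If adverse events cluster in the first weeks after surgery, the loss is smaller than shown. If they rise after a hernia or its repair, it is larger. The documents give no figure for either.

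**The case against.** The strongest reply is that this is only a wording conflict. Item C can be read as ending study visits, with record review to Year 1 continuing in the background. That reading is possible, but item C excludes follow-up without qualification and counts the patient as a completer, so the conflict has to be resolved in the text.

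A reader might infer more: that control patients will be cut short about four times as often and that the safety comparison is therefore biased against SS-PDS. The documents do not support this, for four reasons.

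- The ratio 0.13/0.03 = 4.3 is a ratio of planning assumptions, and the protocol says no earlier study supports the SS-PDS rate. It also counts hernias, not shortened follow-up. A hernia found at the Year 1 visit costs little or nothing.
- The protocol does not commit to crude proportions. Methods that allow for unequal observation time remain open and would reduce the distortion, although they cannot restore uncollected events that follow a hernia.
- The affected endpoint is narrow. Hernia and pain are excluded from objective I. Surgical site infection and wound dehiscence are also excluded, and are followed to Week 4 whether or not a hernia occurs.
- The formal tests under the safety section's Evaluation Methods name A+C against B+D. That is the drain contrast, for which no hernia difference is assumed, and it conflicts with the Overview and objective I. The distortion concerns the suture comparison, not those tests as written.

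The size is also small against sampling error. At an event rate of 30% with 87 per group, the standard error of the difference is √(2 × 0.3 × 0.7/87) = 6.9 points.

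All four limits stand. None removes the contradiction or the dependence of safety observation on the primary outcome.

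**Conclusion.** The point holds as an internal contradiction with a modest consequence. If sites follow item C, later adverse events go uncollected in patients with a hernia. If hernia rates differ as planned, the loss falls mainly on the control group and tilts the suture safety comparison against SS-PDS. A plausible size is about 0 to 2 percentage points, given the planning hernia rates, assumed adverse-event risks of 20% to 60% and a crude comparison. The missed events after a hernia or its repair are a separate loss that cannot be quantified from the documents. A definite bias is not shown. This is a worthwhile correction and does not threaten the primary analysis.

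**What to change.** Reconcile item C of Removal of subjects from study with the adverse-event row of the observation table. Item C would say that a hernia diagnosis ends hernia assessment only. Adverse-event collection would then continue to the planned Year 1 visit and record review, unless the patient leaves under another item of the same section. Items A, D and E (the subject's own withdrawal, another midline laparotomy, noncooperation) would still end participation early, so the change does not give every patient a full year. The ambiguous 4-week wording in item C should be clarified at the same time.

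The cost is a short wording amendment and continued adverse-event follow-up of about 14 patients at most, using a visit and a record review already in the plan. The change concerns data collection only, not treatment.
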